### Sample Size and Statistical Power

This is the first study to investigate the #chatsafe intervention in an RCT and the first to use the proposed measures. As such, there are no previous data to guide the possible effect of the intervention, and therefore the sample size is required; however, a sample of ~400 participants (200 per arm) should be sufficient to assess the primary study outcome with a 5% significance level and 80% power.

The pilot study [13] recruited a total of 507 participants within a 3-month period, resulting in a final sample of 189 young people who completed all 3 time points. Note that the intervention period for this study was 12 weeks compared to 8 weeks in this study. As such, data from the pilot study on rates of recruitment and attrition indicate that the recruitment period of up to 12 months will be more than sufficient to achieve the required sample size.

In an effort to reduce attrition, all participants will be sent a SMS text message by a research team member halfway through the intervention period (week 4), as well as at T2 and T3 if they have not completed their survey 4 days after being sent their survey. This will encourage participants to complete their survey if they have not already done so and will provide them the opportunity to raise any concerns or questions.

### Ethical Considerations

The study has been approved by the University of Melbourne Human Research and Ethics Committee (ID 2022-24238-32907-3). All participants will be required to provide written consent prior to commencement of the study.

The study will be carried out in accordance with the principles contained in the Declaration of Helsinki and the Australian National Health and Medical Research Council (NHMRC) National Statement on Ethical Conduct in Human Research and the NHMRC Australian Code for the Conduct of Research. In addition to being assessed at T2, safety will also be tracked using the weekly evaluation and engagement survey to identify any distress that is attributed to the intervention (see Table 1). Previous distress and suicide risk will be deemed as that reported during the baseline assessment. Further relevant risk will not be reported unless adverse events are reported by the participant or other study team members, which are deemed to possibly having been caused by study activities such as distress because of the intervention or because of interaction with the study team.

As per the pilot study, an SMC has been established. The main purpose of the committee is to oversee the safety of the trial. It comprises the study Chief Investigator (JR), members of the study team, as well as an Orygen Sponsor Operations representative, a statistician, a clinician, and a subject-matter expert. An initial meeting will be held prior to the commencement of recruitment to review the study risk assessment and the determination of safety oversight procedure. The research team will meet fortnightly for the duration of the trial, and a standing function of these meetings will be to review safety incidents and refer any relevant matters to SMC. All members of the SMC will be convened on a study-specific basis (ie, any time a serious safety concern is raised). The SMC will make recommendations as to appropriate risk assessment and mitigation measures, including but not limited to decisions as to whether the study should be amended or put on hold.

Finally, detailed safety protocols have been established and overseen by the trial psychologist (SR) and Orygen’s Sponsor Operations team (Multimedia Appendix 3).

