### Study Outcomes

The primary outcome is safety when communicating online about suicide, as measured via the purpose-designed #chatsafe online safety questionnaire at T2. This measure was specifically designed for this purpose by 3 study authors (JR, [name], and CC).

Secondary outcomes are (1) confidence when communicating on the internet about suicide, as measured via the purpose-designed #chatsafe online safety questionnaire at T2; (2) willingness to intervene against suicide on the internet, as measured via the Willingness to Intervene Questionnaire at T2 [15]; (3) internet self-efficacy, as measured by the Internet Self-Efficacy Questionnaire at T2 [16]; (4) safety of the weekly #chatsafe content, as measured by the purpose-built weekly evaluation and engagement survey; (5) acceptability of the #chatsafe intervention, as measured by the purpose-built T2 evaluation questions; and (6) safety of the #chatsafe social media intervention (as a whole), as measured by the number of (or absence of) adverse events recorded throughout the trial. Participant adverse events include (1) participant response to item 9 on the 9-item Patient Health Questionnaire [17] at baseline (time 1), time 2, or time 3. (2) Participant response to the 9-item weekly evaluation survey indicates distress, measured by participants selecting “very distressed” in response to the question “To what extent did you find the content this week distressing?” (3) Participant response to the T2 evaluation questionnaire indicates that a particular piece of campaign content made them feel distressed or at risk of suicide. (4) The participant directly contacts the research team via social media or email and reports distress or risk of harm to self. All adverse events will be responded to by the study team, in line with the study’s safety management strategy. (7) Feasibility of the #chatsafe social media intervention was measured by campaign reach via social media analytics, and participant retention or attrition via audit of study enrollment and withdrawal logs. (8) Self-reported evaluations of the acceptability of receiving the #chatsafe social media intervention were measured by purpose-designed study questions. Exploratory outcomes are as follows: (1) subgroup differences (gender, age, previous exposure to, previous experiences of suicide and self-harm, and level of social media usage) at T2 and (2) self-reported open-ended evaluations of the safety, feasibility, and acceptability of receiving the PROSPEct social media intervention for sexual health promotion in the control group at T2.

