### Randomization and Treatment Allocation

Participants will be randomized to the intervention or the control group using block randomization with varying block sizes. The allocation ratio will be 1:1. The randomization schedule is computer generated by independent information technology personnel with guidance from the study statistician (MS). The schedule will then be implemented by a member of the study team (other than the statistician) into the REDCap database management software for allocating treatments to individual participants. Except for the study statistician, the study team members are not blinded to the treatment allocations. The study statistician will not have access to the randomization component of the database and will not be informed about the treatment allocations and will therefore remain blinded. As the study statistician will not be involved in any aspect of this study's operations other than data analysis, there are no circumstances we could foresee under which the study statistician would be required to be unblinded.

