### Statistical Analysis

At baseline, state of residence, postcode, age, Aboriginal or Torres Strait Island status, gender identity, sexual orientation, primary language spoken at home, cultural background, and educational and occupational background will be reported using descriptive statistics and will be checked for imbalance between trial arms. The moderating effect of gender (male, female, trans, and gender diverse), age group (ie, 16-20 and 21-25 years), time spent on social media, psychological distress, and previous experience of suicide and self-harm will be considered in analyses as covariates.

Analyses will be performed on an intention-to-treat basis, where all individuals randomized will be included in the analysis by their allocated trial arm status regardless of whether they received all, part, or none of the intended treatments. For the primary analysis, we will use linear regression to estimate the difference in the mean changes between the intervention and control arms at T2 in the outcome safety when communicating online about suicide, as measured via the #chatsafe online safety questionnaire. This analysis will adjust for T1 scores. Multiple imputation will be used to address attrition bias, with 50 imputation samples generated using chained equations. We will conduct 2 sensitivity analyses. One sensitivity analysis will be undertaken using complete cases only (ie, repeating the primary analysis but only analyzing participants who have complete T1 and T2 data). The second sensitivity analysis will use multiple imputation and include the following potential moderating factors as covariates: gender (male, female, transgender, and gender diverse), age group (ie, 16-20 and 21-25 years), time spent on social media, psychological distress, and previous experience of suicide and self-harm.

The secondary outcomes at T2 and T3 will be analyzed based on the primary analysis and the 2 sensitivity analyses. We will use linear regression for continuous outcomes, logistic regression for binary outcomes, and negative binomial regression for counts.

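### The causality condition under Ethical Considerations is absent from the adverse event definition for the safety outcome; if it governs that outcome, a team aware of allocation could record harm differently by arm

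*Protocol article*

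**What the plan says.** **Study Outcomes** makes the safety of the intervention as a whole a secondary outcome (number 6), "as measured by the number of (or absence of) adverse events recorded throughout the trial". It lists four kinds of participant adverse event:

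1. a response to PHQ-9 item 9 "at baseline (time 1), time 2, or time 3";
2. an answer of very distressed to the weekly survey question "To what extent did you find the content this week distressing";
3. a T2 evaluation answer that a piece of content caused distress or a feeling of suicide risk;
4. direct contact with the team to report distress or risk of self-harm.

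None of the four asks the team to judge cause.

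**Ethical Considerations** first classes distress and suicide risk found at baseline as previous. It then states: "Further relevant risk will not be reported unless adverse events are reported by the participant or other study team members", and limits those events to ones "which are deemed to possibly having been caused by study activities such as distress because of the intervention". The research team meets fortnightly, and "a standing function of these meetings will be to review safety incidents and refer any relevant matters to SMC".

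**Randomization and Treatment Allocation** states: "Except for the study statistician, the study team members are not blinded to the treatment allocations".

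**Statistical Analysis** gives a general rule for secondary outcomes, including "negative binomial regression for counts". It does not name adverse events.

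**The concern.** The two sections give different entry rules for what may be the same events. A T2 or T3 item 9 response, or a message reporting suicidal thoughts, is an adverse event under Study Outcomes. Under Ethical Considerations it may go unreported if judged unrelated to the study. The article does not say which rule determines the count for outcome 6.

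This matters because the judgement is open to knowledge of allocation. One arm receives material about suicide and the other material about sexual health, so the same suicidal distress can look related in one arm and incidental in the other. The error could also run the other way, if a team invested in the intervention is slow to attribute harm to it. Blinding the statistician does not help, because an event screened out before recording never reaches the analysis. Randomization protects a comparison of harm only when both arms are counted by the same rule.

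Aims and Hypotheses states as its third hypothesis that the intervention is safe. Neither a null result nor an excess could be read with confidence if recording depended on attribution.

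**Working it through.** The plan gives no figure for the adverse event comparison, so there is nothing to reproduce. The check is a comparison of the text, followed by an illustration.

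**Step 1. The event types against the causality condition.**

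| Type | Source | Link to content in the definition | Team causality judgement in the definition |
|---|---|---|---|
| 1. PHQ-9 item 9 | T1, T2, T3 surveys | none | none |
| 2. Very distressed | weekly survey | in the question asked | none |
| 3. T2 evaluation | T2 survey | in the participant's answer | none |
| 4. Direct contact | participant message | none | none |

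Types 1 and 4 carry no link to study content, so a causality condition could most readily remove these. Types 2 and 3 are tied to content by the participant and leave little for the team to decide.

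**Step 2. Who judges.** Ethical Considerations does not say. The research team reviews safety incidents and decides what to refer, and only the statistician is blinded. The safety monitoring committee includes the Chief Investigator and study team members. No blinded assessor is named. A judgement made with knowledge of allocation is a reasonable inference, not a stated fact.

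**Step 3. Size if the condition operates.** Let both arms have the same true event rate, let q_A and q_B be the shares judged related, and let s be the share of events open to the condition. Then

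observed ratio = (1 − s + s·q_A) / (1 − s + s·q_B).

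The values of q and s are assumptions; the article gives none.

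- s = 1, q_A = 0.80, q_B = 0.60: 0.80/0.60 = 1.33; reversed, 0.60/0.80 = 0.75.
- s = 1, q_A = 0.80, q_B = 0.40: 0.80/0.40 = 2.0; reversed, 0.5.
- q_A = q_B, or s = 0: ratio 1, no bias.

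For 80% v 60%, intermediate values of s give a ratio between 1 and 1.33.

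**Step 4. Simulation of the s = 1 case.** Assumptions: 200 per arm, 8 weekly surveys with 70% returned in both arms, mean event probability 5% per returned survey with log-normal variation between persons (SD 1 on the log scale), no true difference, negative binomial model with dispersion fixed at 1 and robust standard errors, 400 runs.

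| Judged related, A v B | Mean estimated ratio | Share with p < 0.05 |
|---|---|---|
| 80% v 80% | 1.01 | 7.5% |
| 80% v 60% | 1.34 | 20% |
| 80% v 40% | 2.01 | 68% |

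This agrees with the arithmetic. The 7.5% is the rejection rate of this setup with no differential attribution, so the other two rows should be read against it rather than against 5%.

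**Step 5. Baseline events.** Study Outcomes counts item 9 at T1 as an adverse event. Under Participants and Recruitment, T1 is completed before allocation, and Ethical Considerations calls baseline risk previous. A T1 response cannot be an effect of either arm. Counting it adds events that are expected to be equal by arm and pulls the ratio towards 1.

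**The case against.** The strongest reply is that the condition may have nothing to do with outcome 6. The sentence stands under Ethical Considerations, concerns when further risk is reported, and can be read as an escalation rule. Outcome 6 has its own definition without a causality test, three of its four types are participants' own survey answers, and both arms complete the same surveys. The safety strategy in Multimedia Appendix 3, not shown here, may settle the matter. This stands as far as it goes: the text does not show that the condition filters outcome 6, or that all adverse events pass through it. But the text does not exclude that reading either, and outcome 6 counts events as recorded.

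It is also fair to say that the article nowhere states that the unblinded team makes the judgement, and that an arm contrast of adverse events is not expressly announced. The contrast follows only from the general rule for secondary outcomes.

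A reader might go further and infer that unreturned surveys enter the count as zero events, so that the comparison is biased a second time and needs a log(surveys returned) offset. The documents do not support this. Statistical Analysis does not assign negative binomial regression to adverse events by name. It refers secondary outcomes to the primary approach, which uses multiple imputation, with complete cases as a sensitivity analysis; neither sets missing to zero. An exposure term is neither stated nor excluded, and is commonly left to a statistical analysis plan, which is not shown. Such an offset would also be undefined for participants who return no survey, would not suit direct-contact events, and would not cure dropout driven by distress.

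**Conclusion.** The point holds as an inconsistency worth correcting. Two sections give different rules for which events are reported, one of them with a causality condition, in a trial where everyone but the statistician knows the allocation. If that condition determines outcome 6, the comparison of harm **may** be biased.

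Direction and size are unknown. The ratios of 1.33 (80% v 60%) and 2.0 (80% v 40%) rest on assumed attribution shares, equal true rates and all events being open to the condition; they shrink towards 1 as fewer events are open to it and vanish if attribution is equal across arms. To say that the comparison is biased would claim more than the text shows.

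**What to change.** Reconcile Study Outcomes and Ethical Considerations as follows.

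- For outcome 6, record every event of the four listed types that occurs after randomization and report it by arm, regardless of judged cause.
- Show judged relatedness only as a separate descriptive column, and say who judges it; a judge unaware of allocation is preferable.
- Report T1 responses to PHQ-9 item 9 as baseline risk, not as adverse events.
- Print the number of surveys returned by arm beside the counts. Types 1 to 3 can be seen only on a returned survey, and the pilot kept 189 of 507 participants through all time points (189/507 = 37.3%).
- If the causality condition is meant only for escalation, say so.

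The cost is a few sentences and a table. The downside is a larger reported event count. The response to participants and referral to the safety monitoring committee are unaffected.

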### Youth Participation

Young people have been involved in the preparation of this study in multiple ways. First, the entire #chatsafe program of work has been conceptualized, designed, and conducted in partnership with young people. The #chatsafe guidelines were created using the Delphi consensus method, with young people as an expert panel [11]. The first #chatsafe social media campaign was cocreated in partnership with over 140 young people [12].

The study was presented to Orygen’s Youth Research Council in November 2021, and feedback on intervention development and study conduct was obtained. A total of 3 co-design (N=46) and 1 user testing (N=10) workshops were conducted in April and May 2022 to help create the trial content. A total of 3 youth advisors helped to develop the participant information consent form and the #chatsafe online safety questionnaire. Finally, we are currently recruiting 2 paid youth advisors to this study to assist with participant recruitment and engagement. At the end of the study, they will assist with the interpretation and dissemination of the study findings, including conference presentations and journal articles.

## Results

The funding for this project was awarded in November 2020 by the Australian Research Council; however, progress was delayed down due to the impacts of the COVID-19 pandemic. Approval from the University of Melbourne Human Research and Ethics Committee was provided in October 2022. Recruitment into the trial began in November 2022 and study completion is anticipated by June 2024. The trial is registered with the Australian and New Zealand Clinical Trials Registry (ACTRN12622001397707).

## Discussion

This will be the first RCT internationally to test the impact of a social media intervention designed to better equip young people to communicate safely on the internet about suicide.

Social media platforms are commonly used by young people to communicate about suicide. While users rarely set out to cause harm to themselves or others, the potential for harm exists [18,19]. Therefore, it is essential that young people are adequately equipped to safely communicate on the internet about suicide. Guidelines regarding safe reporting of suicide exist for mainstream media [20]; however, until recently, no such guidelines have been developed by, and for, young people. Also, existing media guidelines do not specifically address the challenges and opportunities offered by social media. Although media campaigns are gaining traction in the suicide prevention sector, to date, they have not been developed with young people in mind nor have their impact on behavior change, in particular among young people, been tested.

The development of the #chatsafe intervention not only addresses these gaps, but it also represents a paradigm shift. It shifts the narrative away from advising young people to avoid engaging in suicide-related communication on social media—a strategy that is clearly not working—toward an approach that seeks to better equip young people to communicate safely. The guidelines themselves have already had significant traction not just in Australia but also internationally. They have been adapted for 11 additional countries and downloaded around 120,000 times [21]. In addition to being freely available on the Orygen website, they are also available via both the Facebook and Instagram Safety Centers, thereby significantly extending their reach [22,23]. The social media content has been widely disseminated via platforms such as Instagram, Facebook, Snapchat, and YouTube. There are few suicide prevention interventions that have the potential to be delivered at scale in this way.

This study proposes a rigorous and novel methodology. Until now, research into suicide and social media has been largely cross-sectional in nature and has examined the association between social media use and suicidal thinking. No studies have tested suicide prevention interventions delivered via social media using robust research designs. This study will build on a previous pilot study ([name] et al, unpublished data) and will provide a robust evidence base for this work.

This work is timely. Given the rising rates of youth suicide in Australia and the acceptability of social media among young people, incorporating social media–based interventions into the suicide prevention landscape is an obvious next step. This intervention, if effective, could also be extended to international settings, thereby improving online safety for young people not just in Australia but globally.

## Appendix

Multimedia Appendix 1 Intervention content examples.

Multimedia Appendix 2 The control content.

Multimedia Appendix 3 Overview of safety management strategy.

Multimedia Appendix 4 Peer review reports from the Discovery Projects 2021-2023 - Australian Research Council (Canberra, Australia).

## Abbreviations

NHMRC: Australian National Health and Medical Research Council
RCT: randomized controlled trial
REDCap: Research Electronic Data Capture
SMC: safety monitoring committee
